#### Aim 1: effects of teacher training program on students

Grounded in SDT and CMC, the first aim of this study will be to assess the impact of a teacher training program aimed at enhancing relatedness-supportive behaviors and class cohesion while minimizing relatedness-thwarting behaviors on students’ affective, behavioral, and cognitive outcomes. In line with this aim, three hypotheses will be tested. It is hypothesized that, by Time 2 (T2), experimental group students will perceive improvements in their PE teachers’ relatedness-supportive behaviors (Hypothesis 1), class cohesion, relatedness satisfaction, autonomous motivation, and affective (i.e., problematic relationships), behavioral (i.e., group processing), and cognitive variables (i.e., learning and academic performance; Hypothesis 2) compared to baseline values (Time 1 [T1]) and control group students. Given the lack of previous studies, no specific hypotheses will be formulated regarding the intervention’s long-term effects (Time 3 [T3]) on the study variables. Finally, students’ relatedness satisfaction/frustration and class cohesion, representing an individual-level and a group-level factor, respectively, will serve as mediators in the indirect relationship between the independent variable (i.e., treatment condition) and affective, behavioral, and cognitive outcomes, specifically in autonomous motivation, problematic relationships, group processing, learning, and academic performance (Hypothesis 3, see Figure 2).

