**Figure 2 fig2:**
[figure not shown]
Hypothetical multilevel model of the predictive relationship between the study variables.

Previous correlational studies examining the relationship between students’ perceptions of relatedness support and various outcomes, while accounting for sex differences, have yielded mixed results (Leo et al., 2023b; Leo et al., 2022; Vasconcellos et al., 2020; White et al., 2021). In this regard, although previous studies have included sex as a covariate when analyzing the effects of SDT-based interventions, sex differences are rarely reported for either teachers or students (Vasconcellos et al., 2020). However, systematic reviews and meta-analyses have emphasized the importance of examining school-based motivational intervention effects separately for boys and girls (Vasconcellos et al., 2020). Therefore, it is crucial to account for sex differences when evaluating intervention effects to determine whether they are equally effective for both sexes. Given the inconsistent findings in previous research regarding the study variables, no specific hypotheses will be formulated regarding potential sex differences among students.

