#### Sample recruitment with inclusion criteria

Between 8–10 secondary PE teachers, assigned to the experimental group and to the control group equally, along a subset of their students, will be anticipated to take part in this study. Given the research team’s limited resources, the maximum number of participating teachers will be set at ten. Randomization will be performed using a digital tool. To minimize the risk of cross-contamination between conditions, teachers from the same high school will not participate. Teachers will be recruited through multiple channels, including social media platforms, telephone calls, and emails. Specifically, information (e.g., flyers and recruitment letters) will be shared via professional networks, PE-related social media groups, and the regional government’s official teacher registry. School principals will also be contacted directly to help disseminate the invitation within their schools.

The registration period will last approximately 2 weeks. Teachers whose participation is not approved by their school leadership will not be included. If more than 10 teachers, or multiple PE teachers from the same school, express interest, a waiting list will be created. Final selection will be based on predefined inclusion criteria and logistical feasibility, including school location, number of participants per school, schedule compatibility, and the research team’s capacity to monitor and support the intervention.

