Teachers must meet the following inclusion criteria to participate in this study: (1) be an in-service PE teacher at the same school for the entire academic year; (2) complete the study questionnaires at three different time points; (3) not participate during the entire academic year in other intervention or training programs similar to this study; (4) attend all the training program sessions; (5) allow research team visits for classroom observation; and (6) participate in a focus group at the end of the intervention. Each PE teacher will recruit at least four classroom groups of no fewer than 16 students each, ensuring that at least 80% of the students in each group participate. Eligible students will be those aged 12–18 years from secondary schools. Participation will be completely voluntary and anonymous. School principals and students’ families will also be informed about the study’s aims and characteristics to obtain their informed consent for participation. The 80% participation rate applies only to baseline (T1); teachers not reaching it may be excluded, with replacements drawn from a waiting list. Dropout over time will not lead to exclusion if at least 60% of students complete all data points. The research team will make every effort to retain the full sample and minimize attrition throughout the study. Finally, the inclusion criteria for students’ participation in the intervention program will be: (1) obtaining consent from both parents/legal guardians and students; (2) commitment to completing the questionnaires assessing the study variables three times; and (3) regular participation in PE lessons.

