### Plan of analysis

A mixed-method analysis will be conducted to evaluate the training program, as well as to assess the impact of its implementation in PE lessons on the study variables for both teachers and students. Regarding the quantitative analysis, first, a descriptive analysis will be conducted to evaluate both teachers’ and the external researcher’s perceptions of the training program, assessing aspects such as its innovation, practical relevance, and the feasibility of the strategies implemented. Second, to assess the impact of the intervention program on the study variables for both teachers and students, the nature of the variables will first be examined through tests of normality, validity, and reliability across the three measurements. Third, the assumptions of independence, linearity, and homogeneity of variance will be verified to ensure the appropriateness of analyses based on the general linear model. Fourth, between-group and within-group differences will be analyzed using repeated-measures multivariate analysis of covariance (MANCOVA). A 3 × 2 (Time × Condition) repeated measures MANCOVA will be performed for both teachers and students, with covariates such as age, sex, teaching experience, type of school, and school location for teachers, and age, sex, sociocultural background, and school grade for students. If parametric assumptions are not met, appropriate non-parametric alternatives such as the Wilcoxon signed-rank test (for within-group comparisons) and the Mann–Whitney U test (for between-group comparisons) will be used. Subsequently, to examine intragender differences of the intervention on study variables, a 3 × 2 × 2 (Time x Condition x Sex) repeated measures MANCOVA will be performed for both teachers and students. To further examine changes in each outcome variable over time (T1, T2, and T3) within each group (experimental vs. control), multiple paired t-tests with Bonferroni correction will be conducted. Effect sizes will be calculated using partial eta squared (*η^2^ₚ*). Effect size thresholds will be interpreted as small (*η^2^ₚ* > 0.01), moderate (*η^2^ₚ* > 0.06), or large (*η^2^ₚ* > 0.14) following Cohen’s criteria. For all analyses, the significance threshold will be set at *p* < 0.05. All statistical analyses will be conducted using IBM SPSS Statistics v.25.0. Finally, a longitudinal structural equation model will be employed through the statistical software Mplus (Muthén and Muthén, 1998-2019) to analyze the predictive relationships between the study variables, allowing for the observation of potential differences at the three specific times (T1, T2, and T3) when data are collected.

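### The plan for Hypothesis 3 does not carry over the multilevel structure announced in Aim 1, names no cluster level, and gives no valid test of the condition-to-mediator path with 8 to 10 teachers

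*Protocol article*

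**What the plan says.** Three places in the protocol article describe the mediation model.

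- **Aim 1** makes treatment condition the independent variable. It names relatedness satisfaction/frustration and class cohesion, "representing an individual-level and a group-level factor, respectively, will serve as mediators". The outcomes are listed as "specifically in autonomous motivation, problematic relationships, group processing, learning, and academic performance (Hypothesis 3, see Figure 2").
- **The Figure 2 caption** reads "Hypothetical multilevel model of the predictive relationship between the study variables". The figure itself is not reproduced in the text available.
- **Plan of analysis** says that "a longitudinal structural equation model will be employed through the statistical software Mplus", using the three waves. It states no level, cluster variable or cluster correction.

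Sample recruitment with inclusion criteria sets the design: "Between 8–10 secondary PE teachers, assigned to the experimental group and to the control group equally". It adds that "the maximum number of participating teachers will be set at ten" and that no two teachers come from one school. It also says: "Each PE teacher will recruit at least four classroom groups of no fewer than 16 students each", with at least 80% of each group taking part at baseline.

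**The concern.** Condition does not vary within a teacher. Every indirect effect in Hypothesis 3 begins with the path from condition to a mediator, and that path is a comparison of 4 or 5 teachers with 4 or 5 others, however many students answer the questionnaire.

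The analysis text leaves the level open, and each way of filling the gap has a problem:

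- **Single level.** Students are treated as independent and the standard error of the path is too small.
- **Class as the only second level.** Classes sharing a teacher are treated as independent.
- **Teacher as the cluster.** There are very few units for the model that Aim 1 describes.

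If the first path is falsely significant, and mediators and outcomes correlate among students as expected, mediation is claimed where the training changed nothing. This mechanism is the reason the protocol gives for combining its two theoretical frameworks.

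**Working it through.** **Inputs from the protocol.** 8 to 10 teachers in equal arms; at least 4 classes per teacher, so 4 × 8 = 32 to 4 × 10 = 40 classes; at least 16 students per class, so 64 per teacher and 512 to 640 in all, or about 410 to 512 at 80% participation. At 80%, a class of 16 gives about 13 students and a teacher about 4 × 13 = 52. The threshold is 0.05, taken as two-sided. No ICC, effect size or power is stated for the mediation model, so there is no figure to reproduce.

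**Assumed.** Teacher ICC ρt of 0.02 or 0.05; class-within-teacher ICC ρc of 0.05 or 0.10; no true effect of condition on the mediator; no T1 adjustment.

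**1. Single-level fit.** The variance of a teacher mean is ρt + ρc/4 + (1 − ρt − ρc)/52. Multiplying by 52 gives the design effect DE = 1 + 51ρt + 12ρc. The real type I error is 2[1 − Φ(1.96/√DE)].

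**2. Class as the only second level.** The variance of a class mean is v = ρt + ρc + (1 − ρt − ρc)/13. Two classes of one teacher correlate r = ρt/v. With four classes per teacher the remaining inflation is 1 + 3r, entered in the same formula.

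| ρt / ρc | DE, single level | Type I error | r | 1 + 3r | Type I error, class only |
|---|---|---|---|---|---|
| 0.02 / 0.05 | 2.62 | 23% | 0.14 | 1.42 | 10% |
| 0.02 / 0.10 | 3.22 | 27% | 0.11 | 1.32 | 9% |
| 0.05 / 0.05 | 4.15 | 34% | 0.30 | 1.89 | 15% |
| 0.05 / 0.10 | 4.75 | 37% | 0.23 | 1.70 | 13% |

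Null simulation with 4 classes of 13 per teacher agrees: roughly 22 to 38% for the single-level fit, about 9 to 17% with class only, and about 5% for a t test on teacher means.

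**3. The indirect effect itself.** This was simulated with 64 students per teacher, a mediator-to-outcome slope of 0.4 and no condition effect. The single-level joint-significance test rejected in about 18% of runs at teacher/class ICC 0.01/0.04, 26 to 28% at 0.02/0.05, 37 to 38% at 0.05/0.05 and 49% at 0.10/0.05. With both ICCs zero it rejected in about 5%.

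**4. Teacher as the cluster.** Three mediators (relatedness satisfaction, relatedness frustration, cohesion) and five outcomes give at most 3 + 3 × 5 + 5 = 23 between-level paths. Adding 8 residual variances and 8 intercepts makes 39 parameters; adding 3 + 10 = 13 residual covariances makes 52. If cohesion is the only between-level mediator, there are 1 + 5 + 5 = 11 paths and 11 + 6 + 6 = 23 parameters. All these counts exceed 8 to 10, for one time point.

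**5. What a valid test of the path can detect.** Teacher means have 8 − 2 = 6 to 10 − 2 = 8 degrees of freedom. With 64 students per teacher, power at d = 0.3 is 48 to 60% at ICC 0.02, 29 to 38% at 0.05 and 19 to 24% at 0.10. At d = 0.5 and ICC 0.02 it is 88 to 96%. A randomisation test has C(8,4) = 70 or C(10,5) = 252 allocations, so its smallest two-sided p is 2/70 = 0.029 or 2/252 = 0.008. Significance at 0.05 is therefore attainable.

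**The case against.** A reader might infer more than the document supports, in four ways.

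- **That the protocol states no level for this model.** It does. Hypothesis 3 points to Figure 2, whose caption says multilevel, and Aim 1 assigns levels to the mediators. Mplus is compatible with a multilevel model. The gap is in the Plan of analysis, which does not repeat that structure or say whether the cluster is class or teacher. An article may leave some of this detail to a fuller document.
- **That every reading fails outright.** Class is a natural unit for class cohesion and supplies 32 to 40 clusters. The cohesion-only version, with 23 parameters, is below that number, so a reduced between-class part may be estimable; the full version, with 39 to 52, is at or above it. But class-level clustering alone does not repair the condition path. Nor is a teacher-level test hopeless: for a large effect and a small ICC its power is good.
- **That the model as drawn cannot be estimated.** The figure is not available. The count of 23 comes from the text and is an upper limit, since paths from the individual-level mediators may be within-level.
- **That false mediation findings are certain.** The rates depend on assumed ICCs and omit T1 adjustment, and the largest apply only to a single-level fit, which the caption contradicts.

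The same unit-of-analysis question bears first on the student MANCOVA, of which this is a downstream instance. What remains is that the analysis as written does not match the hypothesis and figure, and that neither a single-level fit nor one clustered on class alone gives a valid test of the first link in the chain.

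**Conclusion.** The concern holds in this limited form, and should be fixed before analysis. The Plan of analysis specifies a longitudinal structural equation model without the multilevel structure of Aim 1 and Figure 2 and without a cluster level, while condition varies only between 8 to 10 teachers. Under the assumed ICCs, type I error on the condition-to-mediator path is roughly 22 to 38% if the model is single-level and about 9 to 17% if only class is modelled, against about 5% for teacher-level inference. With teacher as the cluster, the full Hypothesis 3 model has more between-level parameters than the clusters can support, even when cohesion is the only between-level mediator. The error rates move with the ICCs; the unit of assignment and the number of teachers are fixed by the protocol.

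**What to change.** - Reconcile Aim 1, the Figure 2 caption and the Plan of analysis so that all three describe one multilevel model, and name class and teacher as its cluster levels.
- Reduce the between-level part to what 8 to 10 teachers can support.
- Test the condition-to-mediator path with small-sample teacher-level inference, adjusted for T1 values: teacher summaries with t on 6 to 8 degrees of freedom (fewer if T1 enters as a teacher-level covariate), or a randomisation test.
- Build the interval for the indirect effect from that path, for example by Monte Carlo or a joint-significance rule.
- Label Hypothesis 3 exploratory.

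Fitting one mediator and one outcome at a time is an option, not a required correction; it would replace the joint mediators by up to 3 × 5 = 15 models and raise a multiplicity question. Using T3 outcomes after T2 mediators is also optional, and Aim 1 sets no specific hypotheses for T3.

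The cost is wording and modest analysis work, with no extra data. Conclusions on Hypothesis 3 will be weaker.

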## Discussion

This study protocol describes a training program for in-service secondary PE teachers and their subsequent intervention implementation with students. Based on SDT (Ryan and Deci, 2017) and the CMC (Leo et al., 2023d) theoretical frameworks, the training program is focused on relatedness-supportive and class cohesion strategies while reducing relatedness-thwarting behaviors. The intervention will assess the benefits of the training program for both students and teachers. Additionally, the study will evaluate the quality of the training program from both the teachers’ and an external researcher’s perspective.

This study is expected to contribute to new knowledge in 10 key areas: (1) grounded in SDT and CMC, this will be the first teaching program specifically designed to equip teachers with relatedness-supportive/thwarting and class cohesion strategies within an educational context; (2) the quality of the training program will also be assessed using questionnaires, a focus group involving all PE teachers, and observations by an external researcher; (3) the training program will be implemented not only prior to the intervention phase but also during it through a booster sessions; (4) the training program will also include two individual follow-up sessions, during which constructive feedback will be provided, along with individualized debriefings; (5) promising strategies that have demonstrated effectiveness in previous SDT-based training programs will be employed (e.g., supportive attitude, congruent style, concise theoretical input, co-creation of teaching strategies; Vasconcellos et al., 2020; White et al., 2021); (6) intervention fidelity will be evaluated using an observation instrument aligned with both SDT and CMC frameworks; (7) the TMBs identified by Ahmadi et al. (2023) will be applied during the intervention to determine which specific techniques drive its effects; (8) the effects of the intervention on teacher variables will be evaluated using a mixed-methods approach, including questionnaires and focus group; (9) the differential effects of the intervention on male and female students —and, if feasible, on teachers— will be examined; and (10) a follow-up post-intervention assessment will be conducted to evaluate the long-term impact on the study variables. These 10 key aspects will help future PE researchers and teachers replicate the training program and its implementation in other educational contexts, ensuring its adaptability and feasibility within typical school settings.

In line with these contributions, the effectiveness of the intervention will be examined through a series of research hypotheses. According to Hypothesis 1, students in the experimental group are expected to show greater improvements in their perception of relatedness support and relatedness thwarting from their PE teacher compared to baseline values and the control group students at post-test (T2). Similarly, it is anticipated that experimental group students will show greater improvements in class cohesion, motivational variables (i.e., relatedness satisfaction/frustration and autonomous motivation), and affective (i.e., problematic relationships), behavioral (i.e., group processing), and cognitive variables (i.e., learning and academic performance) compared to baseline values and control group students (Hypothesis 2).

Additionally, it is expected that students’ relatedness satisfaction/frustration and class cohesion will mediate the effect of the program on affective, behavioral, and cognitive outcomes (Hypothesis 3). All these expected outcomes from the first three hypotheses are supported by scientific literature, as correlational evidence suggests that students’ perceptions of relatedness-supportive behaviors are associated with positive outcomes in PE (Leo et al., 2023e; Sparks et al., 2017; Vasconcellos et al., 2020), while relatedness-thwarting behaviors are linked with maladaptive outcomes (Leo et al., 2023e). Similarly, class cohesion (both task and social cohesion) has been positively linked to educational outcomes, such as motivation and classroom engagement (Leo et al., 2023a, 2023f). Although SDT-training programs specifically aimed at for PE teachers that focus on relatedness-need supportive strategies remain scarce, the only identified study in this area has reported some positive post-intervention outcomes, especially among students (Sparks et al., 2017). Thus, by expanding on previous research through the inclusion of relatedness-thwarting behaviors and class cohesion strategies and addressing its limitations, the study expects to achieve the positive outcomes outlined above.

Finally, we expect that teachers participating in the training program will report improvements in their beliefs, perceived feasibility, and intention to apply relatedness-supportive and class cohesion strategies; an increased use of relatedness-supportive behaviors; and greater satisfaction in their relationships with students (Hypothesis 4 and Hypothesis 5). A systematic review by Reeve and Cheon (2021) suggested that, despite the still limited evidence, teachers could also benefit from such interventions in areas like autonomy support, job satisfaction, and their relationships with students.

### Limitations

This intervention faces certain limitations that should be considered. Firstly, although the first part of the training program can be considered brief to ensure that PE teachers effectively integrate these techniques into their PE classes, an excessively long duration could discourage their participation. Nevertheless, a booster session will be scheduled 3 months after the first two sessions of the training program. Secondly, to avoid overburdening students, we will assess their perceptions of teachers’ autonomy- and competence-supportive/thwarting behaviors with a single item to control for its effects in the analysis, which may limit our ability to fully gauge their impact. In contrast, teachers will complete the full set of items for both need-supportive and need-thwarting behaviors to control for these effects in the analysis. Thirdly, while students’ perceptions of class cohesion will be measured using a validated scale (Leo et al., 2023c), we were unable to assess class cohesion support, understood as the specific teacher behaviors aimed at promoting task cohesion (e.g., “The teacher encourages us to help each other during the development of tasks and activities) and social cohesion (e.g., “The teacher encourages us to participate together in activities outside of class.”). Fourthly, to assess the fidelity of the intervention, only two classes will be randomly observed for each experimental group teacher due to a lack of human resources. Finally, although all teachers will receive the same training program, each teacher will need to adapt the strategies to their context, the characteristics of their students, available spaces, material resources, etc. Therefore, the number and intensity of the use of relatedness supportive and class cohesion strategies may vary slightly depending on each group.

